## Abstract

**Background:**

A substantial number of valid outcome measures have been developed to measure health in adult musculoskeletal and childhood disability. Regrettably, national initiatives have merely resulted in changes in attitude, while utilization remains unacceptably low. This study will compare the effectiveness and mediators of two different knowledge transfer (KT) interventions in terms of their impact on changing knowledge and behavior (utilization and clinical reasoning) related to health outcome measures.

**Method/Design:**

Physical and occupational therapists (n = 144) will be recruited in partnership with the national professional associations to evaluate two different KT interventions with the same curriculum: 1) Stakeholder-Hosted Interactive Problem-Based Seminar (SHIPS), and 2) Online Problem-Based course (e-PBL). SHIPS will consist of face-to-face problem-based learning (PBL) for 2 1/2 days with outcome measure developers as facilitators, using six problems generated in consultation with participants. The e-PBL will consist of a 6-week web-based course with six generic problems developed by content experts. SHIPS will be conducted in three urban centers in Canada. Participants will be block-allocated by a minimization procedure to either of the two interventions to minimize any prognostic differences. Trained evaluators at each site will conduct chart audits and chart-stimulated recall. Trained interviewers will conduct semi-structured interviews focused on identifying critical elements in KT and implementing practice changes. Interviews will be transcribed verbatim. Baseline predictors including demographics, knowledge, attitudes/barriers regarding outcome measures, and Readiness to Change will be assessed by self-report. Immediately post-intervention and 6 months later, these will be re-administered. Primary qualitative and quantitative evaluations will be conducted 6-months post-intervention to assess the relative effectiveness of KT interventions and to identify elements that contribute to changing clinical behavior. Chart audits will determine the utilization of outcome measures (counts). Incorporation of outcome measures into clinical reasoning will be assessed using an innovative technique: chart-stimulated recall.

**Discussion:**

A strategy for optimal transfer of health outcome measures into practice will be developed and shared with multiple disciplines involved in primary and specialty management of musculoskeletal and childhood disability.

## Background

Patient-oriented health outcomes are key to assessing health care in chronic illness. Chronic disability, as a result of adult musculoskeletal or childhood disorders, is profound and comprises a large component of practice for a variety of health care providers. Musculoskeletal diseases of adulthood are the leading cause of long-term disability in Canada, accounting for roughly one-third of the country's long-term disability costs [1]. Childhood disorders also account for a large percentage of disability treatment costs with 1 in 12 children now considered disabled; increasing rates are attributable to improvements in medical care that save more compromised children, broader definitions of disability, and a greater willingness to report handicaps [2]. Due to the chronic nature of these disorders, treatment is focused on minimizing disability and improving quality of life. Standardized measurement of the impact of interventions on these health outcomes is fundamental to advancing clinical practice and research.

The current use of patient-oriented outcome measures in research and practice is deficient, despite the fact that health care professionals recognize the importance of measuring health outcomes and efforts have been made to transfer available knowledge into practice. These efforts include national initiatives by the professional associations of both occupational therapists (OT) and physical therapists (PT), traditional workshops [3], published editorials [4], scientific articles [5-16], textbooks [17], professional association endorsements, and promotion of an outcomes database. While agreement with the need for outcome measures is consistently high, utilization remains low across professional groups dealing with these chronic problems, such as Rehabilitation [18], Rheumatology [7,19], and Orthopaedic Surgery [20]. Rehabilitation is commonly performed by PTs and OTs in a variety of practice settings. As few knowledge transfer studies have included these providers, we decided to focus on PTs and OTs for this study. The needs have been well established in this area, and the investigators have established partnerships with the associated national professional associations who will facilitate the current project and arising national KT initiatives.

The deficiency in current practice indicates a failure to implement effective knowledge transfer, and systematic reviews confirm that KT is based on inadequate evidence. The current failure to implement health status measures into practice is not unexpected; reviews of available evidence suggest that traditional dissemination/continuing education has little substantive impact on clinical behavior. A large body of evidence has been developed on the impact of continuing education. Studies of high quality have been synthesized in systematic reviews [21-23]. These reviews have focused on physician behavior, in particular, concrete medical outcomes such as prescription practices that are quite different from rehabilitative interventions. Nevertheless, they do provide some indication of KT approaches that might be used in other areas where evidence is lacking.

Separate reviews have addressed printed education materials, educational outreach visits, local opinion leaders, and continuing education workshops/meetings [21,22,24-27]. Each strategy was shown to lead to a measurable change, although the impact of printed materials was small and of uncertain clinical significance [27]. Neither audit and feedback [28-30] nor conferences [31] made substantial change in practice, with larger effects occurring through occasional outreach visits and use of opinion leaders [32]. Educational outreach visits were investigated in 18 randomized trials that were independently reviewed by two researchers [26] and shows that outreach with supporting materials was more effective than no intervention. Again, physician-prescribing practices were the most common target behaviour. In five separate trials, it was shown that outreach visits with social marketing were most effective when high prescribers were targeted [33-35]. However, little evidence addresses the optimal timing or frequency of outreach or whether changes in practice are maintained over time. A single study [36] included 2-year follow-up and demonstrated that new prescribing behaviours were maintained over time.

Continuing education meetings and workshops were addressed in 32 studies that were judged to be of moderate to high quality and included 2995 health professionals, usually physicians [22]. Interactive workshops were shown to have moderate to large effects in six studies and small effects in four. Combinations of workshop and didactic presentation also were effective, showing moderate or large effects in 12 studies and small effects in seven [22]. Seven studies addressing didactic presentations showed no significant impact. It was suggested that didactic presentations might improve knowledge without impacting on practice, whereas small group discussion and practice might improve skills/behavior. Unfortunately, only a single trial made this comparison and it had inconclusive results. Cochrane reviewers suggested that further (high-quality) studies are required, and they should focus on interactive workshops. They also suggested that future studies should use qualitative processes to clarify how specific attributes of workshops contribute to effects on professional practice [22].

There is a specific lack of knowledge on the impact of knowledge transfer on complex clinical decision-making. The majority of intervention trials attempting to change clinical behavior have focused on the prescribing practices of physicians, limiting the generalizability to clinical practices used to manage chronic musculoskeletal or childhood disability problems. Management of chronic conditions requires that health care professional deal with multi-factorial disability issues by selecting multi-level customized interventions. It is more difficult to assess how KT impacts on clinical decision-making in this situation, as compared to monitoring adherence to prescription recommendations. Beggs and Sumison [37] presented a model that incorporated multi-level evaluation of the long-term benefits of continuing education within a Northern Outreach Program for PT and OT. They proposed a 4-stage model of evaluation. Stage 1 involves participant evaluation of the event. Stage 2 evaluates the affective, cognitive, and psychomotor changes that participants experience as a result of the event; this typically requires a pre-test and post-test of attitudes, knowledge, or specific skills. In Stages 3 and 4, higher levels of evaluation are incorporated. Stage 3 evaluates the extent to which programs change the behavior of the clinician within their practice and requires chart audits and observations. Stage 4 focuses on the client and requires evaluation of the efficiency, effectiveness, adequacy and appropriateness of care and its impact on resultant health outcomes.

We know from surveys of orthopedic practice [18] that the use of standardized health outcome measures is low. Conversely, within pediatric rehabilitation utilization levels are higher, but therapists reported difficulty in selecting and applying available outcome measures appropriately (pilot work, publication under review). It is clear that evaluation of knowledge transfer should measure changes in knowledge, intent, and behavior, but also determine how new knowledge is incorporated into clinical decision-making.

Systematic reviews have highlighted the need to better understand the mediators of knowledge transfer, and previous work has established that a variety of factors may influence the effects of KT [38,39]. However, the mediators are usually only addressed as secondary issues, and few high-quality studies or literature synthesis have been conducted. Prior knowledge, education, and age have been considered as demographic predictors. We will evaluate the role of these previously studied predictors. However, we also wish to identify unknown predictors. To fully address KT mediators, it is important to have an in-depth understanding of responses to knowledge transfer; this requires qualitative research that identifies and characterizes the elements that facilitate or obstruct KT. It is our belief that it is important to identify mediators that could be used to maximize KT effectiveness using a proactive approach. 'Readiness to Change,' also called the Transtheoretical Model, incorporates features of a variety of behavior models to describe the stages of change. It has been used in addiction, health promotion, organizational change, and professional practice literature, most commonly health behavior applications [40,41]. More recently, some have suggested that Readiness to Change may provide a greater depth of understanding of how participants respond to knowledge transfer [42]. Specifically, these investigators used a Readiness to Change questionnaire to evaluate how KT affected intent and action to a short course on knowledge transfer. The Readiness to Change model suggests that change in behavior is modulated by a person's readiness to make changes at the time the information is provided [40,41,43]. In other words, "*the right information and the right process – at the right time.*" The stages are: **Precontemplation **(uninformed about the need for change, uninterested in changing behavior), **Contemplation **(thinking about change in the near future), **Preparation **(ready to make a change in the next month), **Action **(implementing a specific action plan), and **Maintenance **(continuation of desirable actions). The model developers [44-46] and subsequent studies [40,43,47-51] suggest that categorizing people in stages allows one to customize messages and strategies specific to the participant's stage. This concept has not been applied to KT, but if we demonstrate that readiness to change mediates responses in this study, it will provide a promising approach to customize knowledge transfer to users. We will use the qualitative component of the study to understand the decisional balance inherent in the Transtheoretical Model.

Knowledge transfer interventions should bring knowledge into action. Constructivist principles recognize that knowledge is, "not a thing to be sent, but a fluid set of understandings shaped by both those who originate it and by those who use it" [52]. The user is seen as an active problem solver and a constructor of his/her own knowledge rather than a receptacle of information [52]. Clinicians must be able to use outcome measures within a valid and practical framework. Knowledge transfer strategies that engage researchers and clinicians to resolve these competing requirements may be more successful in facilitating the use of outcome measures. The possession of knowledge does not mean that it will be used. The need to go beyond dissemination that simply reflects successful distribution towards effective dissemination that requires use of the information has been emphasized [53]. Huberman [52] differentiated *conceptual use of knowledge*, which is characterized by changes in knowledge, understanding or attitude, from *instrumental use *that includes changes in behavior and practice. Practice surveys indicate both conceptual and instrumental knowledge deficits exist in musculoskeletal and pediatric practice [54]. Knowledge transfer interventions must target and assess both.

McMaster University has a worldwide reputation for educational innovation and problem-based learning (PBL). PBL is an ideal pedagogical strategy for facilitating knowledge transfer. Research on memory suggests memory and learning can be enhanced by: maximizing the positive effects of context by closely matching the learning and clinical environments, enhancing meaning by activating relevant prior knowledge, using educational activities that require the participants to elaborate on their information, and ensuring that new knowledge is used repeatedly in a number of different contexts [55]. The elaboration of information that occurs in tutorial discussion, the use of problems to match new knowledge to the clinical context, and the activation of prior knowledge have been recognized as active components of PBL [56]. Therefore PBL helps in the contextualization of knowledge and in the application of knowledge, which are key components of the CIHR knowledge transfer model (listed as KT3 and KT5 by CIHR).

The rationale for a PBL approach to knowledge transfer is based on solid evidence of adult learning and the effects of PBL [58,59]. This work has shown that PBL is not more effective in acquiring knowledge, but *is *more effective in generating a life-long learning approach where learners become more self-directed in fulfilling their personal learning issues and applying acquired knowledge to problems [58]. This may be the critical component needed in KT, where users must incorporate new knowledge into clinical practice and resolve inherent barriers before implementing change.

Research on KT strategies suggests that the strategy must be tailored to the types of decisions that clinicians face and to the environments in which they work [60]. It is important to consider organizational and political factors that may influence decisions to incorporate new knowledge [60]. Therefore, the curricular design of both knowledge transfer strategies will incorporate contextual learning principles within a PBL framework. Research on both adult education and on effective knowledge transfer suggests that passive learning is ineffective and that interactive strategies are necessary to be successful [60]. While both the interventions will be problem-based and involve interaction, the strategies will differ in the delivery mode. One strategy will incorporate face-to-face PBL, whereas the other will be internet-based. Hence, the nature of interaction will be quite different between delivery modes.

Traditionally, PBL is highly dependent on face-to-face interaction. Effective knowledge transfer is supported through these types of interactions, particularly if associated with an opinion leader [32]. The opportunity for meaningful engagement between researchers developing outcome measures and clinicians using them through a traditional PBL process should augment KT that supports "instrumental use." There is a strong body of evidence supporting the effectiveness of traditional face-to-face PBL education that suggests it will assist clinicians to acquire higher level reasoning, incorporate newly acquired information, and address barriers to implementing new outcome measures [56,59,61]. It is unclear whether the inherent value of face-to-face interaction with developers outweighs the time constraints of this form of knowledge transfer. Research on PBL indicates that learners are initially inefficient and stressed with this new approach to learning [62]. While the learning curve is steep, it is not unattainable. Participants in our pilot study reported that the PBL was time-consuming, but valued.

A rapidly evolving mode of accessing information and continuing education is through the use of the Internet. Online course work has proliferated at a pace well beyond the capacity of educational/KT researchers to study its effectiveness or implications. While theoretical papers on online learning have laid out the pedagogical issues, few high-quality research studies have addressed learning outcomes in a quantitative way. A recent study reviewed all studies indexed on Medline that addressed Internet-based medical education [63] to determine the extent of formal evaluation. Of 85 studies, 55 merely described the program and provided no evaluation. Of the remaining 31 studies, 81% evaluated participant satisfaction, 52% evaluated learning outcomes, and only 6% evaluated change in clinical practice behaviors.

Despite the low level of evidence surrounding online professional education, there is a rationale for this approach. One potential benefit is that participants can access information/course work asynchronously. If participation in face-to-face PBL is a significant barrier to busy clinicians, online interaction might be preferable. There are advantages to online learning that may promote knowledge transfer. For example, online learning allows for increased time for reflection and synthesis [64,65] and provides increased time to develop the ability to organize thoughts when problem-solving collaboratively [64]. Online learning and online forums also are thought to promote critical thinking and problem-solving in a collaborative environment [66]. Despite these potential benefits, few studies have specifically examined online PBL. Dennis [67] compared online PBL and face-to-face PBL and found there was no difference in learning outcomes. However, the online groups spent more time on learning, suggesting that this process was less efficient. Chan et al. [68] randomized family physicians to either Internet-based PBL or a control group (Internet content without PBL) and found no difference in knowledge. However, the sample was small (n = 23). In a qualitative study, Valaitis et al. (2005) examined health science students' perceptions of online PBL. The results showed that students valued the flexibility of online learning and felt it enhanced their ability to deeply process content, but they had initial difficulties adapting to an online environment and perceived a heavy workload. Given the current state of practice and knowledge, we propose to evaluate two KT approaches to implanting knowledge on outcome measures.

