### Secondary objectives

1. To identify the key elements of SHIPS and e-PBL that engage participants in KT and assist them in addressing barriers to change;

2. To determine whether clinicians exhibit a decisional balance and spectrum of behaviors consistent with the Transtheoretical Model of (Readiness to) Change; and

3. To determine the relative importance of potential predictors of change, including characteristics of clinicians (years of practice, highest degree, Readiness To Change), practice settings (practice type, caseloads, years of experience), and how they affect knowledge acquisition and implementation following KT interventions.

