### Study measures

#### Baseline measurement of eligibility, status, and potential KT predictors

Participants will be pre-screened to ensure inclusion criteria. Eligible participants will then complete a baseline knowledge pre-test (to avoid ceiling effects/lack of responsiveness). Participants also will complete a baseline information questionnaire to collect demographic data, practice patterns, and educational background. Survey measures of knowledge and behavior will be administered. This data collection also will include a measurement of the therapist's intent to use outcome measures, their general level of research utilization, and their readiness to change. This scale evaluating Readiness to Change [40,41,73] was developed to reflect the core elements of the five stages of change, but was specifically applied to changing clinical practice. Although all participants will have agreed to allocation during informed consent, they will be asked their preference with respect to e-PBL and SHIPS so that post-hoc analyses can determine the importance of educational preference as a mediator of response.

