## Analyses

### Quantitative analyses

All data will be double-entered in SPSS 14.0. Descriptive analyses will be conducted, including checking for outliers, normality testing, and univariate correlations. The first primary analysis (Objective 1) will be a two-way repeated measures analysis of variance to determine primary unadjusted differences in absolute scores over time, and between groups for each of the three primary outcome measures: knowledge, utilization, and chart-stimulated recall scores. An analysis of covariance will be used to compare these same effects adjusting for baseline knowledge score, Readiness to Change, years of practice, and educational preference. These analyses across the e-PBL and SHIPS groups will determine the relative effectiveness of these two alternative knowledge transfer choices. Effect sizes and their 95% confidence intervals will be calculated to determine whether there are differential impacts on change in knowledge, utilization, and integration of knowledge between the two different KT approaches. For the secondary research question (Objective 2.3) on the relative importance of KT predictors, a multiple linear regression [79,80] will be used to develop models of how years of practice, educational background, caseload characteristics, educational preferences, or Readiness to Change predict changes in knowledge, utilization, or integration following knowledge transfer interventions, with KT method as a covariate.

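### The regression meant to rank predictors of change leaves out baseline knowledge and age, which the Background says will be evaluated, and three measures that the protocol labels as predictors

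*Protocol article*

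**What the plan says.** Four places in the Protocol article name predictors of response to knowledge transfer, and two models in Quantitative analyses use them.

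- Background, after naming prior knowledge, education and age: "We will evaluate the role of these previously studied predictors".
- Abstract, Method/Design: "Baseline predictors including demographics, knowledge, attitudes/barriers regarding outcome measures, and Readiness to Change will be assessed by self-report".
- The section headed "Baseline measurement of eligibility, status, and potential KT predictors" collects a "measurement of the therapist's intent to use outcome measures, their general level of research utilization, and their readiness to change".
- Secondary objectives, item 3, lists "characteristics of clinicians (years of practice, highest degree, Readiness To Change), practice settings (practice type, caseloads, years of experience", introduced as examples rather than as a closed list.
- Quantitative analyses assigns that objective to a multiple linear regression of how "years of practice, educational background, caseload characteristics, educational preferences, or Readiness to Change predict changes in knowledge, utilization, or integration", with the intervention as covariate. Separately, an ANCOVA of the three primary outcomes adjusts for baseline knowledge, Readiness to Change, years of practice and educational preference.

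The Background also says what is meant to follow. If Readiness is shown to mediate response, it is to be a basis for tailoring knowledge transfer to users.

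**The concern.** The regression is the analysis assigned to the relative importance of predictors, and it can rank only what it contains. Two of the three predictors whose role the Background undertakes to evaluate are not in it, and neither are three further measures labelled as predictors elsewhere.

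The missing baseline knowledge score matters in its own right, because one of the modelled outcomes is change in knowledge. A model of change without its baseline lets any predictor related to baseline pick up part of the baseline effect. For the other omitted measures, the stake is how a Readiness coefficient is read: Readiness is the only measure of willingness to change in the list, and the Background attaches a practical conclusion to it.

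**Working it through.** **1. The lists side by side.**

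| Predictor | Named as predictor in | Objective item 3 | ANCOVA | Regression |
|---|---|---|---|---|
| Prior (baseline) knowledge | Background; Abstract | no | yes | **no** |
| Education | Background | yes | no | yes |
| Age | Background | no | no | **no** (years of practice is in both models) |
| Attitudes/barriers | Abstract | no | no | **no** |
| Intent to use outcome measures | Baseline measurement | no | no | **no** |
| General research utilization | Baseline measurement | no | no | **no** |
| Readiness to Change | Background; Abstract; Baseline measurement | yes | yes | yes |

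Five named predictors are absent from the regression, and four of them are absent from both models. The ANCOVA holds knowledge and Readiness together. It is directed at the intervention comparison, however, and lacks educational background and caseload, so it does not supply the ranking.

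**2. Change without baseline.** Assume equal variance σ² before and after, and a pre-post correlation ρ. Then Cov(post − pre, pre) = ρσ² − σ² = −(1 − ρ)σ², which is negative whenever ρ is below 1. A predictor that rises with baseline knowledge therefore inherits a negative association with knowledge change when baseline is left out. The eligibility rule (a pre-test score of 75% or more is excluded) narrows the range of baseline scores but does not remove this. For utilization and integration, the role of prior knowledge is an empirical question, and it is the one the Background says will be answered.

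**3. Sample size available.** The protocol's 64 per group reproduces: with effect size 0.50, two-sided 0.05 and 0.80 read as power, the t-test gives 63.77, so 64 per group and 128 in total; 128/0.9 = 142.2. At 128, counting one term per variable:

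- Regression as listed: 5 predictors + intervention = 6 terms; 128/6 = 21.3 participants per term.
- With baseline knowledge: 7 terms, 18.3 per term; with age as well: 8 terms, 16.0.
- Second step with three more: 10 terms, 12.8 per term; 11 terms if age is included, 11.6.

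Variables coded as categories would use more terms.

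**4. Illustration of what omission could do (all inputs assumed).** Suppose Readiness has no direct effect and correlates r with an omitted trait whose standardised effect is g. Its apparent coefficient is b = r × g. With N = 128, noncentrality 128b²/(1 − b²) and F on 1 and 121 degrees of freedom, the chance of p < 0.05 is:

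| r | g | b | chance |
|---|---|---|---|
| 0.3 | 0.2 | 0.06 | 10% |
| 0.3 | 0.3 | 0.09 | 17% |
| 0.5 | 0.2 | 0.10 | 20% |
| 0.5 | 0.3 | 0.15 | 40% |
| 0.7 | 0.2 | 0.14 | 36% |
| 0.7 | 0.3 | 0.21 | 67% |

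The protocol gives neither r nor g. The width of the range shows that the size is unknown.

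**5. Price of adjustment (assumed values).** Take a Readiness coefficient of 0.25, residual variance 0.85 and 10 terms. The noncentrality is 128 × 0.25² × (1 − R²)/0.85, where R² is the share of Readiness explained by the added scales. For R² = 0, 0.25 and 0.50 this gives 9.41, 7.06 and 4.71, and power of 86%, 75% and 58%.

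**The case against.** The strongest reply has four parts.

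- The Background's undertaking covers only knowledge, education and age. Knowledge is in the ANCOVA, education is in the regression, and years of practice largely stands in for age. This stands for education and mostly for age. It does not put knowledge into the analysis that assesses relative importance.
- The regression largely follows the objective's own list, which does not name intent, attitudes or research utilization. Some of these measures may also serve as outcomes: the Background wants change in intent evaluated, and the Abstract has baseline measures repeated. Collecting them is therefore not by itself a commitment to use them as regressors. This is fair, but the Abstract and the baseline section heading do label them as predictors.
- A condensed article need not give every covariate. True, but this one gives a specific list, and that list disagrees with its other sections.
- Adjusting Readiness for intent and attitude may remove part of the construct. The Background defines the stages partly by lack of interest and by near-term readiness to act. This stands, and it is why the adjusted estimate should not simply replace the unadjusted one.

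A reader might go further and infer that any Readiness effect from this trial would be spurious, or could not be told apart from intent and attitude. The documents do not support that. They give no correlations or effect sizes, the ANCOVA already pairs Readiness with baseline knowledge, the other measures are to be collected so the model can be extended, and the overlap may be part of what Readiness means.

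**Conclusion.** The mismatch is in the text and should be reconciled. The regression for the third secondary objective omits baseline knowledge and age despite the Background's undertaking, and omits attitudes/barriers, intent and research utilization despite their labels. As listed, it models change without baseline knowledge and cannot rank these five against Readiness to Change. Baseline knowledge is the clearest gap and age the weakest.

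No figure for confounding of Readiness can be derived from the protocol; the 10% to 67% above depends wholly on assumed values. The point is confined to a secondary objective and to the use the Background makes of Readiness. It leaves the SHIPS versus e-PBL comparison and the sample size untouched.

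**What to change.** 1. Add the baseline knowledge score, which the screening test already provides, to the regression in Quantitative analyses.
2. State that years of practice represents age, or add age as a term, and make the Background agree.
3. Fit a second-step model that adds attitudes/barriers, intent and general research utilization. Report the Readiness coefficient and its added R-squared both with and without these scales. Say in advance that the two answer different questions, because the scales overlap in content with the stages.
4. Align the predictor lists in the Abstract, Background, Secondary objectives, baseline measurement section and Quantitative analyses.

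The cost is one or two terms in the first model and three more in the second, on data the protocol already plans to collect (age is presumably among the demographic items, though the baseline section does not name it). The downside is wider intervals for Readiness in the second step, and the loss is not trivial if overlap is strong: in the assumed example, power falls from 86% to 75% or 58%. Keeping the first-step estimate alongside preserves the more precise figure.
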